### Sensitivity of results to missing data

We expect that for a proportion of patients it will not be possible to measure outcome scores at 12 and/ or 15 months and that some data will be missing. The described mixed model will be fitted using maximum likelihood methods that are valid under the missing at random (MAR) assumption.[64] However, this assumption relates to the variables that are included in the model. To allow for a variable predicting “missingness”, this variable needs to be included as either one of the explanatory or dependent variables of the mixed model. We will perform three sensitivity analyses for violations of the assumptions of MAR to assess the sensitivity of the results to missing outcome data:

In the first sensitivity analysis we will use the method of multiple imputations.[64] Data handled using multiple imputation will be imputed 100 or more times, applying a set seed using the ice package in STATA version 11.0 [65]. In this procedure missing data is filled in using other information which has been observed on patients. For our analysis, the imputation model will include all variables which we believe may contain information about the missingness mechanism at 12 and 15 months and must include all variables that will be used in the main analysis model [66]. We account for clustering by including cluster indicators in our imputation model [67]. Each of these completed datasets can then be analysed using the proposed statistical modelling and the estimates from the linear mixed model will be drawn from the average of analysis of each of the completed datasets using Rubin’s Rule [64].

Analysis of data where the outcome is incomplete always requires the untestable assumptions about the missing data that they are missing at random. We, therefore, will perform a second sensitivity analyses to explore the effect of departures (varied over a plausible range) from the assumption of missing at random made in the main analysis as recommended by White et al [68]. For example, to assess for differential drop-out in patients between treatment groups a sensitivity analysis would assume that the cases lost to follow-up have systematically worse outcome than completers and outcome will be worse in treatment group and we will assess the effect of different values on the treatment differences at 12 months.

We also anticipate drop-out of care-coordinators. In a further sensitivity analysis we will perform the same analysis as described for the Intent-to treat sample using the patients whose care coordinator did not drop out. This analysis assumes that care coordinators drop-out is completely at random (MCAR) to obtain unbiased results. We will analyse the reasons for drop-out of care-coordinator and participants using a qualitative approach which allows us to assess the validity of this assumption.

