### Sample size

The power analysis is performed for the two subscales measures, Physical and Mental health components of SF-36 Quality of Life scale.[43] We have assumed a common standard deviation of the change scores between baseline and 12 month follow-up of 10 for the Physical component score and 12 for the Mental health component score (based on the QUATRO study [60]), supplemented with further information sought directly from the study team (project reference: QLG4-CT-2001-01734, European Union)) and a cluster size of 4 patients per care coordinator with intraclass correlation of 0.05. Using 80% power, a 5% alpha level and two-tailed assumptions, a sample size of 56 care coordinators and 216 patients are needed to detect a clinical significant difference of 5 points in Mental Health Component change score (Cohen’s d = 0.42), between two groups and a sample size of 38 care coordinators and 152 patients are needed to detect a clinical significant difference of 5 points in Physical Component change score (Cohen’s d = 0.5) between two groups. Assuming a drop-out rate of 20% of the care-coordinators and their patients and an additional patient drop-out rate of 30%, a total sample size of 98 care coordinators and 392 participants are needed for the Mental health score and 70 care coordinators and 280 participants for the Physical health score.

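### Imputing with one indicator per care coordinator does not match the random coordinator effect in the analysis model, and overstates the standard error of the multiple-imputation sensitivity analysis

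*Protocol article*

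**What the plan says.** All of this is in the Methods of the protocol article.

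- **Sensitivity of results to missing data.** The section announces: "We will perform three sensitivity analyses for violations of the assumptions of MAR". The first is multiple imputation with the Stata ice package, at least 100 imputations and Rubin's rules. Its imputation model "must include all variables that will be used in the main analysis model", and on clustering the text says "We account for clustering by including cluster indicators in our imputation model". The second analysis varies departures from MAR over a plausible range. The third keeps only patients whose coordinator stayed, and the text says that it rests on MCAR.
- **Intention-to-treat sample.** The analysis model has arm, time, their interaction, borough and baseline scores as fixed terms, and care coordinator as a random factor. Patients are to be followed up even if their coordinator drops out.
- **Selection and randomisation.** Coordinators are the randomised unit, stratified by borough.
- **Sample size.** The planning values are "a cluster size of 4 patients per care coordinator with intraclass correlation of 0.05", and an SD of change of "12 for the Mental health component score". The loss allowance begins "Assuming a drop-out rate of 20% of the care-coordinators and their patients", with a further 30% of patients on top. The target for the mental component is 98 coordinators and 392 participants.

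**The concern.** The imputation model and the analysis model treat the coordinator differently. A random effect pulls each coordinator's mean strongly towards the overall mean when clusters are small and the ICC is low. An indicator does no pulling: the coordinator's mean is whatever the few observed patients give. Every imputed value in that cluster is centred on this noisy mean, so the completed data look far more clustered than the real data. The random-coordinator model fitted afterwards then reads the noise as true between-coordinator variance.

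At stake is what the sensitivity analysis tells the reader. It should show what happens when the missing-data handling changes. Here the interval also widens because of the indicators, so real fragility cannot be told apart from an artefact. The description adds to this: standard multiple imputation itself assumes MAR, yet it is listed among analyses for violations of MAR.

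**Working it through.** **1. The plan's own figure.** The mental-component target reads: "Using 80% power, a 5% alpha level and two-tailed assumptions, a sample size of 56 care coordinators and 216 patients are needed". The effect behind it is 5 points.

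- Per arm without clustering: 2 × (1.96 + 0.8416)² × 12² / 5² = 90.4, so 91.
- Design effect: 1 + (4 − 1) × 0.05 = 1.15, and 91 × 1.15 = 104.7 per arm. That is 27 coordinators of 4 per arm, or 54 coordinators and 216 patients.
- The 216 is reproduced. The stated 56 coordinators would be 56 × 4 = 224 patients, a small mismatch that does not affect this point.
- Retention: 0.8 × 0.7 = 0.56, and 216 / 0.56 = 386, close to the stated 392.

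**2. Variance components.** Total variance is 144. Between coordinators: 0.05 × 144 = 7.2. Within: 136.8.

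**3. What indicator imputation does to one cluster.** Let r of the 4 patients be observed. The estimated cluster mean has sampling variance 136.8/r, and drawing the indicator's coefficient for each imputation adds another 136.8/r. The covariance between two patients of the completed cluster is:

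- observed–observed: 7.2
- observed–imputed: 7.2 + 136.8/r
- imputed–imputed: 7.2 + 2 × 136.8/r

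The average over the six pairs is the between-coordinator variance that the analysis model sees. The between-imputation variance of the cluster mean, with m = 4 − r missing, is (m/4)² × 136.8/r + (m/16) × 136.8.

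| r | Probability at 30% patient loss | Average pair covariance | Between-imputation variance |
|---|---|---|---|
| 4 | 0.2401 | 7.2 | 0 |
| 3 | 0.4116 | 30.0 | 11.4 |
| 2 | 0.2646 | 75.6 | 34.2 |
| 1 | 0.0756 | 212.4 | 102.6 |
| 0 | 0.0081 | – | – |

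Weighted over clusters with at least one observed patient, the apparent between-coordinator variance is 50.5 against a true 7.2, and the between-imputation variance is 21.7.

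**4. Standard error.** With 49 × 0.9919 = 48.6 usable coordinators per arm:

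- Reported SE by Rubin's rules: √[(50.5 + 136.8/4 + 1.01 × 21.7) × 2/48.6] = 2.09.
- Actual sampling SE of the same estimate: the average of 7.2 + 136.8/r is 63.1, and √(63.1 × 2/48.6) = 1.61.
- Power: Φ[(5 − 1.96 × 2.09)/1.61] = about 71%.

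The reported SE therefore exceeds even the estimator's own sampling SE.

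**5. Simulation.** The set-up was 98 coordinators of 4, SD 12, true effect 5, 100 imputations, Rubin's rules and a REML random-coordinator analysis, with 400 to 500 trials per scenario. Assumptions: one time point, six boroughs, no baseline or 15-month predictor.

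| Scenario | Method | SE | Power | Significant main results lost |
|---|---|---|---|---|
| 30% patients lost | Likelihood mixed model | 1.53 | 91% | – |
| | Imputation, indicators | 2.09–2.10 | 70–72% | 22–23% |
| | Imputation, random effect | 1.55 | 91% | about 1% |
| 20% coordinators and 30% patients lost | Likelihood mixed model | 1.72 | 82% | – |
| | Indicators, empty clusters left out | 2.35 | 57% | 31% |
| | Indicators, empty clusters given the reference coordinator of their arm and borough | 2.57 | 50% | 40% |
| | Imputation, random effect | 1.75 | 80% | 2% |

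The apparent between-coordinator variance under indicators was about 51 to 64. Mean estimates under indicators were 4.92 to 5.00, and type I error was 1% to 2%.

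**6. Range.**

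- With 10% of patients missing, the SE ratio to the likelihood model is 1.13 and 4% of significant results are lost.
- With ICC 0.15 and the planned loss, the ratio is 1.31 to 1.39 and 26% to 40% are lost.
- A further simulation (200 trials per scenario, 30% patient loss) added the baseline score and an assumed residual correlation of 0.6 between 12 and 15 months. With baseline only, the ratio was 1.36. When a third to a half of the patients missing at 12 months had a 15-month score, it was 1.26 to 1.30, and 12% to 17% of significant results were lost.

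**The case against.** Several points on the other side are fair.

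- **Collinearity.** A reader might infer that the fault is that arm and borough are exact combinations of the coordinator indicators. They are, because coordinators are nested in both. But dropping redundant columns leaves the predictions unchanged for every coordinator with an observed patient, and the inflation appears with no coordinator lost. The cause is the unshrunk mean.
- **Lost coordinators.** A reader might take the 20% allowance to mean that a fifth of the indicators cannot be estimated. That is a planning allowance. The intention-to-treat section continues follow-up after a coordinator drops out. If that succeeds with 30% patient loss, only 0.3⁴ = 0.8% of coordinators have no outcome. The protocol does not say how empty clusters would be imputed, so no single worst-case figure is warranted. The no-coordinator-loss result is the one that fits continued follow-up, and it already shows the problem.
- **Simplified simulation.** The real imputation model would hold baseline and 15-month scores. These reduce the inflation but do not remove it (26% to 30% under the assumed correlation).
- **Limited consequence.** The estimate is unbiased, the test errs on the conservative side, the primary maximum-likelihood analysis is unaffected, and no decision rule hangs on this p-value. All of that stands. It makes false fragility a risk, not a certainty.
- **Labelling.** The text notes that MAR is relative to the variables in the model, and the imputation model adds predictors of missingness. So the first analysis can probe MAR given only the main model's covariates. It still assumes MAR given the richer set. The third analysis is already described as MCAR and needs no relabelling.

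**Conclusion.** The concern holds in this form: coordinator indicators in the imputation model do not match the random coordinator effect in the analysis model, and they make the multiple-imputation SE too large for technical reasons. At planned missingness the inflation over the likelihood model is about 37% to 50%. It is about 26% to 30% at 30% patient loss if 15-month scores help, and about 13% if only 10% are missing. At planned missingness, roughly 12% to 40% of results significant in the main analysis would turn non-significant here, against 1% to 2% with random-effect imputation.

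The documents do not support saying that the trial's result would be biased, that the primary analysis is at risk, or that a real effect would necessarily look fragile.

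The sizes rest on the protocol's planning values and on reading cluster indicators as dummy variables. They also rest on the assumed six boroughs and the assumed 12- to 15-month correlation. The upper end further depends on coordinators with no outcomes and on how they are imputed. This should be changed, though it does not threaten the main conclusion.

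**What to change.** In the section Sensitivity of results to missing data, replace the coordinator indicators with a multilevel imputation model: a coordinator random intercept; arm, borough and baseline physical and mental component scores as fixed terms; and the 12- and 15-month scores imputed jointly, with the planned predictors of missingness as auxiliary variables. In the simulation, random-effect imputation brings the SE back to 1.55 against 1.53 for the likelihood model (30% patient loss), and to 1.75 against 1.72 with coordinator loss as well.

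Describe this analysis as one under MAR with auxiliary variables, so that only the second analysis is presented as testing departures from MAR.

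The cost is different imputation software, a sentence or two of text and more computing time. No data collection or sample size changes.

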### Complier average causal effects (CACE)

In addition to the standard intention-to-treat analysis we will estimate a measure of the treatment impact only for compliers. Specifically, we will employ complier average causal effects (CACE), where randomisation indicator is used as an instrumental variable to evaluate the causal effect of HPI in the subpopulations that are considered compliers to treatment. [69]This complier average causal effect is of scientific and policy interest, because it assesses the intervention effectiveness of the treatment when it is in fact taken (treatment efficacy).

### Economic evaluation

The economic evaluation will be from two perspectives: health/social care and societal (the latter additionally includes production losses due to time off work for those in employment).

To estimate HPI costs, relevant staff will document resource inputs (care coordinator training/supervision and intervention sessions with study participants). Other resource use data will be collected retrospectively by participant self-report using specifically designed interviewer-administered questionnaires at baseline, 12 months (each for the previous 6 months) and 15 months (previous 3 months). Unit costs will be attached to all resource use to estimate individual-level total costs.

Costs and outcomes will be described by arm and assessment point but the economic evaluation will focus on 15-month findings in the form of cost-effectiveness analyses based on SF-36 mental and physical component scores and cost-utility analyses based on quality-adjusted life years (QALYs). QALYs will be calculated by applying UK general population utility weights to the SF-36 [43](via the SF-6D) [70] with adjustment for relevant period of time and linear interpolation to calculate the area under the curve.

Costs and QALYs will be reported as mean values per arm with standard deviations. Differences between arms will be tested by multi-level modelling to accommodate cluster randomisation.

Given two cost perspectives and three outcome measures, there will be 6 cost-outcome combinations to consider. For combinations suggesting one arm having additional costs alongside improvements in outcomes, incremental cost-effectiveness ratios (ICERs) will represent the additional cost per additional unit of outcome. Uncertainty will be explored using incremental cost-effectiveness planes and cost-effectiveness acceptability curves (CEACs) based on the net benefit approach [71]. CEACs will represent the likelihood of the HPI being cost-effective relative to the control given different monetary values for incremental improvements in SF-36 and QALY outcomes. CEACs will be based on bootstrapped (to account for non-normally distributed data) regressions of arm upon net benefits, controlling for clusters. Sensitivity analyses will explore consequences for cost-effectiveness/utility results if key assumptions are altered (e.g. HPI unit costs, imputation for loss of follow-up).

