**Methods:**

Impact therapy will be delivered by care coordinators in the community to the treatment group and will be compared to treatment as usual (TAU). The main hypothesis is that the addition of IMPACT Therapy (HPI) to TAU will be more effective than TAU alone in improving patients’ quality of life as measured by the Short Form-36, including mental health and physical health subscales on completion of the intervention at 12 months post randomisation. A subsidiary hypothesis will be that addition of IMPACT Therapy (HPI) will be more cost-effective than TAU alone in improving health in people with SMI 12 months from baseline. The IMPACT therapy patient groups’ improvement in quality of life, as well as its cost effectiveness, is hypothesised to be maintained at 15 months. Outcomes will be analyzed on an intention-to-treat (ITT) basis.

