### Objectives

The primary objective is to determine the effectiveness and cost-effectiveness of the addition of an intensive health promotion intervention (IMPACT Therapy), designed to improve physical health and reduce substance use, to usual mental health care delivered by care coordinators (TAU) in people with severe mental illness (SMI) (defined as schizophrenia (ICD-10 code: F20), delusional Disorder (F22.0), schizoaffective disorder (F25), bipolar affective disorder (F31), recurrent depressive disorder (F32), current episode severe with psychotic symptoms (F33.3)).

The main hypothesis is that the addition of IMPACT Therapy (HPI) to TAU will be more effective than TAU alone in improving patients’ quality of life as measured by the Short Form-36, including mental health and physical health subscales [43] on completion of the intervention at 12 months post randomisation. This 12 month period incorporates an initial 3 months post randomisation to train the care coordinators to provide the IMPACT Therapy (HPI) over the following 9 months. We also hypothesise that the effect will be sustained three months after the end of the intervention, at 15 month follow up.

Our secondary hypothesis is that the addition of IMPACT Therapy (HPI) will be more cost-effective than TAU alone in improving health in people with SMI 12 months from baseline and that this cost-effectiveness will be sustained 3 months later at 15-month follow-up.

Subsidiary Hypotheses include

1. TAU plus IMPACT Therapy will reduce waist circumference by at least 1 cm at one year, compared to TAU alone

2. TAU plus IMPACT Therapy will be more effective in reducing weight at one year, compared to TAU alone

3. TAU plus IMPACT Therapy will result in a 50% reduction in proportion of people using cannabis compared to TAU alone.

4. TAU plus IMPACT Therapy will be more effective in reducing symptoms of psychosis compared to TAU alone

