## Methods

### Design

A multicentre, two arm, parallel cluster randomized controlled trial (RCT) of an health promotion intervention, (HPI) IMPACT Therapy. The study was planned and implemented in concordance with the Consolidated Standards of Reporting Trials (CONSORT) cluster trial extension standards [44,45] to compare the cost-effectiveness of combining treatment as usual (TAU) plus IMPACT Therapy, versus TAU alone in improving health at one-year follow-up. Figure 1 summarises the trial design.

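### The cost-effectiveness hypothesis is set at 12 months and sustained at 15, but the economic analysis focuses on 15 months and specifies no test at 12

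*Protocol article*

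**What the plan says.** The Objectives section of the protocol article gives the secondary hypothesis as IMPACT Therapy plus TAU being "more cost-effective than TAU alone in improving health in people with SMI 12 months from baseline and that this cost-effectiveness will be sustained" at the 15-month follow-up. The abstract's Methods paragraph has the same time point ("more cost-effective than TAU alone in improving health in people with SMI 12 months from baseline") and adds maintenance at 15 months. The Design section sets the cost-effectiveness comparison "versus TAU alone in improving health at one-year follow-up".

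The Economic evaluation section is arranged differently. "Costs and outcomes will be described by arm and assessment point", but then "the economic evaluation will focus on 15-month findings in the form of cost-effectiveness analyses", together with cost-utility analyses on QALYs. QALYs are built from the SF-6D with "linear interpolation to calculate the area under the curve". The section adds: "Given two cost perspectives and three outcome measures, there will be 6 cost-outcome combinations to consider". ICERs, planes and CEACs follow from those combinations. None is assigned to 12 months.

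**The concern.** The hypothesis has a main part at 12 months and a maintenance part at 15 months. The analysis section puts its weight on 15 months and leaves the main part without a named cost-effectiveness analysis. Two things are at stake.

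First, whether IMPACT Therapy is cost-effective at the end of treatment would either go unanswered or be answered by an analysis chosen after the data are seen.

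Second, a cumulative QALY at 15 months mixes what was gained during treatment with what happened afterwards. A favourable 15-month cost-utility result could be taken as evidence of persistence when most of it was accrued before month 12.

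**Working it through.** **Step 1: the count of analyses.** The inputs are in the Economic evaluation section: two cost perspectives and three outcomes (SF-36 mental score, SF-36 physical score, QALY).

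- One time point: 2 × 3 × 1 = 6, which reproduces the article's figure.
- Two time points: 2 × 3 × 2 = 12.

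The stated six fits a single time point. Of the six, 2 × 1 = 2 use QALYs and 2 × 2 = 4 use SF-36 scores.

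**Step 2: what a 15-month QALY says about maintenance.** The Outcome measures section gives assessments at 0, 12 and 15 months. Assume a utility difference between arms of 0 at baseline, d at 12 months and r·d at 15 months. The article gives no value for d, and the ratios do not depend on it. Linear interpolation gives:

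- Gain over months 0–12 = (0 + d)/2 × 12/12 = 0.5d
- Gain over months 12–15 = (d + r·d)/2 × 3/12 = 0.125(1 + r)d
- Total at 15 months = 0.5d + 0.125(1 + r)d

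| Effect at month 15 | r | 15-month total | Share accrued by month 12 |
|---|---|---|---|
| Fully kept | 1 | 0.750d | 67% |
| Half kept | 0.5 | 0.6875d | 73% |
| Gone | 0 | 0.625d | 80% |
| Fully reversed | −1 | 0.500d | 100% |

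With the effect gone, the 15-month total is 0.625/0.75 = 83% of the fully kept value and 0.625/0.5 = 1.25 times the 12-month gain. The total reaches zero only at r = −5, because 0.5 + 0.125 × (1 − 5) = 0.

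For assumed d of 0.02, 0.04 and 0.06, the totals in QALYs are:

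- effect gone: 0.0125, 0.025 and 0.0375
- effect fully kept: 0.015, 0.030 and 0.045

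**Step 3: the SF-36 combinations.** If the 15-month score is the outcome, a benefit lost by month 15 appears as no incremental effect, so false persistence is not the risk. The risk runs the other way: a benefit present at 12 months that then fades would be missed, although 12 months is where the hypothesis sits.

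**Step 4: cost data.** By the Economic evaluation section, the 12-month questionnaire covers the previous 6 months and the 15-month questionnaire the previous 3. Self-reported resource use is therefore observed for 6 of the 12 months (50%) by month 12, and for 6 + 3 = 9 of 15 months (60%) by month 15. Months 0–6 are missing from both totals.

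**The case against.** The strongest reply is that the article says *focus*, which does not exclude a 12-month analysis. The count of six names perspectives and outcomes as its factors, not time, so the same set could be repeated at 12 months. Arm differences in costs and QALYs are also to be tested with multilevel models, with no time point attached. All of this is correct. A reader might infer that the economic analyses are confined to 15 months and that neither part of the hypothesis can be answered. The documents do not support that reading. What stands is narrower: no 12-month ICER, plane or CEAC is specified, and separate tests of costs and of QALYs are not a test of cost-effectiveness.

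A reader might also infer that the whole economic evaluation could report persistence after the benefit had gone. That holds for at most the two QALY combinations. In addition, the Intention-to-treat sample section already plans SF-36 treatment differences with confidence intervals at both 12 and 15 months, so a vanished SF-36 effect would be visible beside the economic results.

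It can fairly be said that *sustained* may mean still cost-effective over the longer horizon, and that nowhere does the article say a favourable 15-month CEAC will be taken as proof of persistence. That reading is tenable, but the article does not state it, and it still leaves the 12-month part without a specified test. Nor do the QALY ratios show how far an ICER, net benefit or CEAC would move, since that also depends on incremental cost.

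Finally, a 12-month analysis is not a plain rerun, because of the months 0–6 gap in self-reported resource use. The gap is proportionately larger at 12 months, but the 15-month total has it too, so it is no reason to leave 12 months out.

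**Conclusion.** The concern holds as a mismatch between the stated hypothesis and the specified analysis. The hypothesis is at 12 months with persistence to 15; the cost-effectiveness and cost-utility analyses focus on 15 months, and neither a 12-month test nor a 12-to-15-month comparison is specified. Because the article fixes both the hypothesis and the analysis focus, this is more than a detail left to the analysis plan.

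On size: for the two QALY combinations, complete loss of effect by month 15 lowers the cumulative gain by only 17% from its fully sustained value (0.625d against 0.75d), so that gain discriminates poorly between persistence and loss. This rests on equal baseline utilities, linear interpolation as planned, and a positive d; it concerns QALYs and not costs. For the four SF-36 combinations, the statement in Step 3 rests on 15-month scores being used.

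The point touches a secondary hypothesis and should be put right. It does not affect the primary effectiveness analysis.

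**What to change.** Either of two changes would reconcile the sections.

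1. **Keep the hypothesis and specify its test.** Pre-specify 12-month ICERs, planes and CEACs as the test of the hypothesis in Objectives. Keep the 15-month cumulative analysis as a longer-horizon result. Judge persistence on the month 12–15 increments in cost and QALYs by arm and on the SF-6D difference at 15 months, read alongside the 15-month SF-36 differences already planned.
2. **Restate the hypothesis** as cost-effectiveness over 15 months, and align the abstract, Objectives and Design with it.

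The first option lets the trial answer the question it poses. It costs a second set of economic results (12 combinations in place of 6) and a stated rule for self-reported resource use in months 0–6, which the 15-month total needs as well. It requires no new data collection. The second costs wording alone, but gives up the end-of-treatment question and, for QALYs, any separate statement about persistence.
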